## Abstract

**Background:**

Dysphagia can lead to serious complications such as aspiration and aspiration pneumonia, timely and effective rehabilitation training can improve the swallowing function of patients. However, the conventional rehabilitation training methods used in clinical settings have shortcomings such as poor adherence of patients. We present the study design of a randomized controlled trial that evaluated whether video-game based swallowing rehabilitation training can effectively improve swallowing in patients with dysphagia and whether it has additional benefits compared with conventional training methods to improve swallowing function and training compliance among patients with dysphagia.

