## Objectives {7}

This study aimed to investigate the effect of video-game on swallowing function in patients with dysphagia through a randomized controlled trial. It is hypothesized that video-game based intervention will improve swallowing function better in patients with dysphagia compared to conventional dysphagia training.

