#### Intervention

The intervention was given once a day for 30 min per session, 5 times a week for 4 weeks. The experimental group received the video-game intervention and the control group received the conventional therapy intervention. Both groups received the usual care, including daily feeding education, position training, breathing control, improving cough technique, and thermal tactile stimulation. The researcher will participate in the patient's first three rehabilitation sessions to help guide the patient on rehabilitation methods, and the next 17 sessions will be done independently by the patient (Fig. 1).

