### Strategies to improve adherence to interventions {11c}

Video-game based swallowing rehabilitation programs are safe with multiple game components, so high compliance with the program is expected. Adherence is based on the actual completion of the patient's swallowing function training. The actual completion of the dysphagia training by patients, including the number of training sessions completed and the duration of the training, is objectively recorded by the researcher. In addition to this, participants will be asked to complete a daily training diary in which they record the training activities they perform and record the duration, intensity, and symptoms of discomfort.

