Secondary outcomes in this study were quality of life, nutritional status, satisfaction and adherence. The swallowing quality of life (SWAL-QOL) questionnaire consists of 10 subscales and a symptom scale (14 items) to assess the severity of dysphagia symptoms. Scores range from 0 to 100, with lower scores indicating greater impairment of quality of life from dysphagia [24]. Body mass index (BMI) and Mini Nutritional Assessment Short Form (MNA-SF) were used to assess the nutritional status of the dysphagia patients. BMI is one of the most commonly used nutritional assessments among adults [25]. MNA-SF is commonly used to screen patients for malnutrition or risk of malnutrition with high sensitivity and specificity [26]. MNA-SF in combination with BMI showed higher accuracy [27]. The satisfaction questionnaire was designed based on the literatures. There are 15 items, involving 3 dimensions: training mode content setting, training mode format setting, and self-subjective feeling, and scored on a 5-point Likert scale. The higher the score, the more satisfied the patients were with the video-game training. Adherence was considered good if the patient could complete more than 80% of the training sessions of the corresponding training program; average if the patient could complete 50% to 80% of the training sessions; and poor if the patient could complete less than 50% of the training sessions. Patients are considered to have completed their training when they have completed more than 12 training sessions [28].

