## Statistical methods

### Statistical methods for primary and secondary outcomes {20a}

An intention-to-treat analysis will be performed, and the last available measurement will be used when data were lost due to dropout. Statistical analysis will be performed using SPSS 29.0. Statistical significance of all outcome variables will be established at *P* < 0.05.

All continuous data will be tested for normality, and nonparametric tests will be used for non-normally distributed data. Data conforming to normal distribution will be expressed as mean ± standard deviation (SD), and data with non-normal distribution will be expressed as median (interquartile range).

Comparisons of continuous data of two groups at the same time will be analyzed using independent samples t tests or rank sum tests, and comparisons of two groups of rates will be performed using chi-square test or Fisher exact test [31].

Comparison of continuous data trends over time between different groups at different times, if data normality is present, we will perform a series of repeated measures analysis of variance (ANOVA) for each outcome measure to assess differences between time (4 weeks and 1 month post) and between study groups, as well as interactions between time and study groups. For these analyses, the assumptions of sphericity and homogeneity of variances are tested using Mauchly and Levene tests [32]. If the assumption of sphericity is violated, the Huynh–Feldt correction is applied [32].

If the normality assumption is not met, the linear mixed model will be used for analysis, the comparative analysis at each time was performed using the nonparametric statistical Mann–Whitney U test and its own control two-way comparison using the nonparametric statistical Kruskal–Wallis rank sum test [33].

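### Adherence, a secondary outcome, is defined only as three bands although sessions completed (0–20) are recorded; how much power this costs depends on the attendance pattern

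*Protocol article*

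**What the plan says.** The Intervention section sets the dose of training at "30 min per session, 5 times a week for 4 weeks", that is 5 × 4 = 20 sessions. The section on strategies to improve adherence {11c} says that actual completion, "including the number of training sessions completed and the duration of the training, is objectively recorded by the researcher". A count from 0 to 20 therefore exists for each patient, along with the time spent.

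Outcomes {12} lists the outcome: "Secondary outcomes in this study were quality of life, nutritional status, satisfaction and adherence". It then defines adherence by bands only: good above 80%, poor below 50%, and "average if the patient could complete 50% to 80% of the training sessions". It also sets a separate threshold for having completed training, more than 12 sessions.

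Statistical methods {20a} gives t tests or rank sum tests for continuous data and says "comparisons of two groups of rates will be performed using chi-square test or Fisher exact test". It names no test for ordered categories and does not mention adherence.

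The abstract's background asks whether the game has "additional benefits compared with conventional training methods to improve swallowing function and training compliance among patients with dysphagia". The hypothesis in Objectives {7} is narrower: "video-game based intervention will improve swallowing function better in patients with dysphagia compared to conventional dysphagia training". Sample size {14} rests on the Functional Oral Intake Scale alone.

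**The concern.** Out of 20 sessions, the bands are 0–9 (poor), 10–16 (average) and 17–20 (good). A patient with 10 sessions counts the same as one with 16, while 16 and 17 count as different. If the grades are then compared by chi-square or Fisher, a shift from poor to good is treated no differently from any other rearrangement of three unordered labels. Detail is lost twice: once in the banding and once in the choice of test.

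Poor adherence to conventional training is part of the reason given for the trial. No power was reserved for adherence in a sample of 78, so a real gain in attendance could be missed although the recorded counts would show it. The bands also give no direct answer to the practical question of how many more sessions patients complete.

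**Working it through.** **Inputs from the article.** 20 sessions; bands as above; 1:1 allocation; 31 per group before dropout. The planned size follows from 31 / (1 − 0.20) = 38.75, rounded up to 39 per group, so 2 × 39 = 78. The article states no power, expected attendance or spread for adherence, so there is no adherence figure to reproduce.

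**Assumptions.** Everything below on attendance is assumed. Tests are two-sided at 0.05, with 1,500 to 3,000 simulated trials per scenario.

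**Smooth pattern 1: beta-binomial.** Each patient has an attendance probability p ~ Beta(mc, (1 − m)c) and completes X ~ Binomial(20, p) sessions. Mean m is 0.85 vs 0.75, and a smaller concentration c means more spread between patients. Power (%) at 39 per arm:

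| c | Bands, chi-square | Bands, ordinal rank test | Count, Welch t | Count, rank sum |
|---|---|---|---|---|
| 4 | 43 | 54 | 62 | 68 |
| 8 | 58 | 68 | 79 | 81 |
| 12 | 67 | 77 | 88 | 89 |

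- Chi-square against Welch t loses 62 − 43 = 19, 79 − 58 = 21 and 88 − 67 = 21 points.
- Of that, ignoring order costs 54 − 43 = 11, 68 − 58 = 10 and 77 − 67 = 10 points.
- Banding itself costs 62 − 54 = 8, 79 − 68 = 11 and 88 − 77 = 11 points.
- At 31 per arm, chi-square gives 33, 46 and 56% against 55, 71 and 80% for the rank sum test on the count, a loss of 22, 25 and 24 points.
- With no difference between arms, chi-square rejects in 3–5% of trials and the rank sum test in 4–5%, so the gap is not bought with false positives.

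**Smooth pattern 2: rounded normal.** With 31 per arm, SD 4 and means of 14 vs 17 sessions, power is 81% (t) or 80% (rank sum) on the count, 71% for an ordinal test on the bands and 60% for chi-square. Against the t test the loss is 21 points: 10 from banding and 11 from ignoring order.

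**Range over smooth patterns.** Across rounded-normal scenarios, chi-square loses about 9–27 points. Across beta-binomial scenarios with control attendance of 60–80%, and the effect set so that the rank test on the count has about 80% power, it loses 14–24 points against the t test and 16–34 against the rank sum test. Roughly 10 to 30 is a fair summary.

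**Early-quit pattern.** Some patients stop at a random point in the course and the rest attend nearly everything. Power (%) at 39 per arm:

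| Quitters | Attendance of the rest | Bands, chi-square | Bands, ordinal | Count, t | Count, rank sum |
|---|---|---|---|---|---|
| 10% vs 30% | 95% vs 90% | 74 | 80 | 78 | 97 |
| 10% vs 40% | 95% vs 95% | 78 | 86 | 79 | 64 |

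In the first row the rank test gains greatly, because it picks up small differences among patients who persist. In the second row those patients differ only by noise, and the rank test falls 78 − 64 = 14 points below the bands. In this family chi-square loses 1–8 points against the t test; against the rank sum test the result runs from 32 lost to 14 gained. A further early-quit set gave 71–81% for chi-square on the bands, 64–70% for the rank sum test and 84–87% for Welch t on the count. Together, the loss against the t test is roughly 1 to 17 points.

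**The case against.** The strongest reply is that the criticised analysis is partly inferred. The statistical section does not assign chi-square or Fisher to adherence. The same section offers t or rank sum tests that could be applied to the count, and the article never says the count will go unanalysed. The grades could be read as labels on a measured quantity, with the test left to an analysis plan that is not shown. This stands as far as the choice of test goes: a reader might infer that the article commits adherence to an unordered test, and it does not. It does not remove the point, because the article does fix the outcome definition, and that definition is the three bands.

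Second, a reader might infer a flat loss of about 20 points. The documents give no attendance data, and the size changes with the assumed pattern. About half of it would be recovered by an ordinal test on the same bands. In the second early-quit row that ordinal test (86%) even beats the t test on the count (79%). So the count is not the more powerful choice everywhere, and the rank sum test is not a safe replacement by itself.

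Third, a reader might take adherence for one of the trial's main questions because the abstract names compliance beside swallowing function. The outcome list makes it secondary, and neither the hypothesis nor the sample size covers it. No stated power is breached and the primary comparison is untouched.

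**Conclusion.** The point holds in a limited form. The plan records a 0–20 count, defines adherence only as three bands, and names no categorical test that respects their order. Under smooth attendance distributions the cost is roughly 10 to 30 points of power for chi-square on the bands against a test on the count, about half from ignoring order. Under early-quit patterns it is roughly 1 to 17 points against a t test on the count, and the rank test on the count can be better or worse than the bands. All of these figures rest on assumed attendance, not on anything in the article. The matter concerns a secondary, unpowered outcome and does not threaten the primary conclusion, but it is worth correcting because the better measure is already collected.

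**What to change.** In Outcomes {12}, define adherence as the number of sessions completed out of 20. In Statistical methods {20a}, state that its mean is compared between groups by the t test already in the plan, in the Welch form, with the difference in sessions and a 95% confidence interval, and that the rank sum test is a sensitivity analysis. Keep good, average and poor as a descriptive table; if the bands are tested, use an ordinal test. While editing, explain how the threshold of more than 12 sessions relates to the bands, since a patient with 13 to 16 sessions has completed training yet is graded average.

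The cost is a few sentences. No new data or visits are needed, and the Trial status section places the trial before recruitment. The only downside is that the bands become descriptive.

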### Participant timeline {13}

The participant timeline was presented in Table 1. (Table 1 was placed at the end of the document text file).

**Table 1 Tab1:**
[figure not shown]
Time schedule of enrollment, interventions, and assessments

### Sample size {14}

The sample size was calculated from a previous study conducted by Park et al. [29] in dysphagia patients, which measured patient swallowing function on the Functional Oral Intake Scale (FOIS), with mean of 5.40 and 4.40, SDs of 1.70 and 0.80 for the intervention and control groups, respectively. For a significant level of 0.05 and power of 90%, 31 participants were estimated in each group (62 participants). Finally, to avoid loss of power due to potential dropout, the sample size was increased by 20% for each group, resulting in a total number of participants of *N* = 78. The sample size was estimated using G-Power 3.1 [30].

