## Trial design {8}

This study is a single-center, single-blind, parallel randomized controlled trial (RCT) with a 4-week intervention and a 4-week follow-up. All phases are conducted according to the SPIRT reporting guidelines [18]. Treatments received will be randomly generated by R software in 1:1 numbers, randomly assigned by a postgraduate student not involved in the assessment and intervention, and placed in opaque closed envelopes. The intervention program will be based on the protocol of this study.

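### On the printed inputs, 31 per group gives 90% power in a two-group t test only if it is one-sided; on the conventional two-sided reading power is about 83%, and 90% takes all 78 recruited

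*Protocol article*

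**What the plan says.** Sample size {14} draws its assumptions from an earlier dysphagia study, "which measured patient swallowing function on the Functional Oral Intake Scale (FOIS"). The values it takes from that study are a mean of 5.40 against 4.40, and "SDs of 1.70 and 0.80 for the intervention and control groups". The result follows: "For a significant level of 0.05 and power of 90%, 31 participants were estimated in each group (62 participants"). A 20% allowance for dropout then brings the total to 78. The tool is named ("The sample size was estimated using G-Power 3.1"), but the test selected in it and the number of tails are not. Allocation is equal: "Treatments received will be randomly generated by R software in 1:1 numbers" (Trial design {8}).

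Statistical methods {20a} sets one threshold, a P value below 0.05, for every outcome ("Statistical significance of all outcome variables will be established at" that level). It plans t tests or rank sum tests between groups at each time, chi-square or Fisher tests for rates, and repeated measures ANOVA for group, time and their interaction. No section declares a one-sided test. The hypothesis under Objectives {7} is worded in the direction of the video game being better.

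**The concern.** The section prints every input for a two-group comparison of means, so the result can be checked. The check matches 31 per group with a one-tailed setting and misses clearly with a two-tailed one. An unqualified P < 0.05 is conventionally two-sided, and the group and interaction F tests in a repeated measures ANOVA have no direction. On that reading the stated 90% is not the power of the test that will be reported.

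At stake is the justification for the trial's size. A null FOIS result would be read against a 10% risk of missing a true 1-point difference, when that risk could be as high as 17%. The allowance for dropout would also be used up in reaching 90% power in the first place.

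**Working it through.** **Inputs**, all from Sample size {14} unless noted: means 5.40 and 4.40 (difference 1.00); SDs 1.70 and 0.80; alpha 0.05; power 90%; 31 per group; 20% dropout; 1:1 allocation (Trial design {8}).

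**Effect size.** Root-mean-square SD = sqrt((1.70² + 0.80²)/2) = sqrt((2.89 + 0.64)/2) = sqrt(1.765) = 1.3285. So d = 1.00/1.3285 = 0.7527.

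**Power formula.** For a two-group t test with n per group, power comes from the noncentral t distribution with 2n − 2 degrees of freedom and noncentrality d × sqrt(n/2). At n = 31 the noncentrality is 0.7527 × sqrt(15.5) = 2.963 with 60 degrees of freedom. The critical value is 1.671 one-sided and 2.000 two-sided.

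**The plan's own figure.** One-sided at 0.05, n = 30 gives 89.2% and n = 31 gives 90.06%. The smallest n reaching 90% is 31, as printed. Dropout: 31/(1 − 0.20) = 38.75, rounded up to 39 per group, 78 in total, also as printed.

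**The same inputs, two-sided at 0.05:**

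| Evaluable per group | Power |
|---|---|
| 31 | 83.0% |
| 35 | 87.4% |
| 38 | 89.9% |
| 39 | 90.7% |

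The two-sided requirement is therefore 39 evaluable per group, 78 in total. Holding 90% after a 20% loss would take 39/0.80 = 48.75, so 49 per group or 98 in total.

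**Sensitivity to method at 31 per group, two-sided.** The normal approximation gives 84.2%, Welch's test 82.5%, and the rank sum test about 81.2% (using its efficiency for normal data).

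**Sensitivity to the SD.** The simple average of the SDs (1.25, d = 0.80) gives 28 per group one-sided and 34 two-sided. SD 1.70 alone gives 51 and 62; SD 0.80 alone gives 12 and 15. None of these gives 31 two-sided.

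**A repeated-measures route.** For a non-directional between-group test on m measurements with common correlation ρ, the noncentrality is N × (d/2)² × m/(1 + (m − 1)ρ). At N = 62, m = 2 with ρ = 0.6 gives m/(1 + (m − 1)ρ) = 2/1.6 = 1.25, and m = 3 with ρ = 0.7 gives 3/2.4 = 1.25. Both yield 90.3% power. Both correlations are assumptions; the article states none.

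**Baseline adjustment.** Dividing the residual SD by its unadjusted value leaves a factor sqrt(1 − ρ²), so d becomes 0.7527/sqrt(1 − ρ²). Two-sided power at 31 per group is then 88.9%, 92.0% or 95.4% for assumed baseline correlations of 0.4, 0.5 or 0.6.

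**The case against.** **Sidedness is inferred.** A reader might infer that the article commits to two-sided testing and then contradicts itself. It does not say so. The hypothesis is directional, t and rank sum tests can be run one-sided, and the chi-square tests concern rates rather than FOIS means. This stands as a limit on the claim. It does not remove the point: a directional hypothesis is not a declaration of one-sided testing, and the unqualified threshold and the F tests favour two-sided.

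**One-sided testing is not the only possible origin of 31.** The repeated-measures calculation above also reaches 62 without a one-sided test. This stands as a possibility, so the one-sided match is claimed only for a single-time t test. The article gives no correlation or number of measurements for the sample size, and its Discussion says that the correlations between measurement times are something the trial will help to estimate. The printed inputs support only the two-group comparison.

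**The loss may be smaller than 20% of the information.** A reader might infer that the trial will run at 83% power and that the dropout allowance is worthless. That would require the full loss, no replacement and an analysis of completers only. Sections {20a} and {20c} plan intention-to-treat with last available values and multiple imputation, and section {11b} allows a patient with too much lost data to be replaced. These may recover part of the loss, although imputation does not restore full information. So 83% is the lower end of a range, not a forecast.

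**Conclusion.** The concern holds in limited form. On the printed inputs, 31 per group and 90% power agree in a two-group t test only if the test is one-sided, which the article never declares and which its planned analyses do not suggest. Two-sided, 31 evaluable per group gives about 83%, seven points below the stated figure, and 90% needs all 78 recruited to be evaluable. Power lies between 83.0% and 90.7%, depending on how much information is lost.

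This rests on three assumptions: the printed means and SDs, a single-time comparison of means, and the conventional reading of an unqualified 0.05 threshold. The documents do not show that the trial is too small to be useful, that its type I error is affected, or that recruitment must rise.

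**What to change.** In Sample size {14}, state that the test is two-sided at 0.05 and restate the power as about 83% with 31 evaluable per group and about 90.7% with 39, keeping N = 78. If the figure came from a repeated-measures calculation, say so and give the number of measurements and the assumed correlation. This costs wording only; the stated power becomes less favourable and no patients are added.

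Optionally, make the primary FOIS comparison baseline-adjusted and state the assumed correlation. This is more than wording: it changes the primary analysis, and Methods for additional analyses {20b}, which rules out adjusted analyses, would have to be amended. The gain depends on the correlation, and at 0.4 the power with 31 per group (88.9%) still falls short of 90%.

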### Recruitment {15}

All patients with dysphagia who meet the inclusion criteria are eligible to participate. The study will recruit patients at the rehabilitation center by distributing posters and leaflets containing information about the study. We will collaborate with doctors and rehabilitation therapists, request their help in promoting publicizing the study after the clinic treatments. In addition to this, we will actively promote the study to patients in the wards.

